## **METHODOLOGY**

### **Sample size**

**180**

### **Type of study design**

Open, realistic, prospective, randomized, controlled, interventional clinical study.

### **Participant recruitment process**

Subjects must meet the inclusion criteria and have none of the exclusion criteria in order to be eligible for randomization in this study. Subjects who meet all eligibility criteria, and have signed informed consent will be included under Baseline study visit. Once the subject is randomized the Sponsor Representative or the Study Investigator will provide the study staff with a unique randomization number for the subject. At the Randomisation, subjects will be centrally, dynamically randomised in a 1:1:1:1:1:1 fashion to each of the following six groups, namely two controls and four trial groups each with 30 subjects.

1. Group 1: Control group for Pre-Diabetes (30 subjects).
2. Group 2: Study group for Pre-Diabetes (30 subjects).
3. Group 3: Control group for Type II DM (30 subjects).
4. Group 4: Study group for Type II DM – Study drug will be administered as add on therapy with Allopathic medicines (30 subjects).
5. Group 5: Study group for Type II DM – Study drug will be administered as add on therapy with AYUSH medicines (30 subjects).
6. Group 6: Study group for Type II DM – Study drug will be administered along with life style management (30 subjects).

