| REFERENCE THERAPY                                  | Placebo and Standard of Care (SOC) will be given to control groups. In the study groups the trial drug and SOC will be                                                                                                                                                                                                                                                                                                                                                                                                                       |

|                                 |                                                                                                                                                                                                                                                                                                                                                                                                                                                                                                                                                                                                                                                                                                                   |
|---------------------------------|-------------------------------------------------------------------------------------------------------------------------------------------------------------------------------------------------------------------------------------------------------------------------------------------------------------------------------------------------------------------------------------------------------------------------------------------------------------------------------------------------------------------------------------------------------------------------------------------------------------------------------------------------------------------------------------------------------------------|

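### Type 2 diabetes has one control group with undefined standard of care against three study groups on different named backgrounds, so most or all product contrasts mix background with DiabetEaze

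*Protocol*

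**What the plan says.** The Protocol, under Participant recruitment process, allocates subjects to six groups "each with 30 subjects". Groups 1 and 2 are a control and a study group for pre-diabetes. Group 3 is the only control for type 2 diabetes, and its entry names no background treatment. The three type 2 diabetes study groups are described as follows:

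- Group 4: "Study drug will be administered as add on therapy with Allopathic medicines"
- Group 5: "Study drug will be administered as add on therapy with AYUSH medicines"
- Group 6: "Study drug will be administered along with life style management"

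The Clinical Trial Summary, under Reference Therapy, says "Placebo and Standard of Care (SOC) will be given to control groups". For the other arms it says "In the study groups the trial drug and SOC will be" given. SOC is not defined there or elsewhere in the text. The objectives, both primary and secondary, concern DiabetEaze Powder itself and not a package of care.

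**The concern.** A placebo control isolates the effect of a product when the two arms differ only in the product. Here one control arm has to serve three study arms whose background care differs by design. Where the background in Group 3 differs from that in a study group, the contrast changes two things at once, and a difference (or its absence) cannot be put down to DiabetEaze.

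Two gaps in the text make this worse. First, the summary and the group list together leave unclear what background care Groups 3 to 6 receive: SOC could be the named background of each group, or something common to which the named therapy is added. Second, subjects are said to be "centrally, dynamically randomised in a 1:1:1:1:1:1 fashion to each of the following six groups, namely two controls and four trial groups". Disease status cannot be randomised, so that sentence cannot be meant literally across all six groups. The reader cannot tell whether background treatment is also an existing characteristic or is assigned with the group. If it is assigned, the randomised contrast is a package. If it is already in place, the study groups may not be randomised against Group 3 at all.

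**Working it through.** **Inputs from the protocol.** Six groups of 30; four of them in type 2 diabetes (Groups 3 to 6); significance at p ≤ 0.05. The plan's total reproduces: 6 × 30 = 180. The type 2 diabetes part is 4 × 30 = 120. The protocol gives no effect size, SD or power. Two-sided testing, 80% power and the background differences below are therefore assumptions.

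**Step 1: matching of backgrounds.** This takes the three named backgrounds to be genuinely different, as the separate groups imply.

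| Reading of SOC in Group 3 | Study groups with a fully matched control | Contrasts that mix background and product |
|---|---|---|
| One regimen, equal to one of the three backgrounds | 1 | 2 of 3 |
| One regimen, equal to none of them | 0 | 3 of 3 |
| A mixture of backgrounds | 0 as a whole group; matched subsets only | 3 of 3, unless restricted to subsets |
| Common SOC everywhere, named therapy added on top | at most 1 | at least 2 of 3 |

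Under any single-regimen reading the unmatched study groups hold at least 2 × 30 = 60 of the 120 subjects.

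**Step 2: what a mixture would leave.** If Group 3 were split evenly, each background would have 30 / 3 = 10 controls. By normal approximation the difference detectable with 80% power is (1.96 + 0.84) × √(1/n₁ + 1/n₂):

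- 10 versus 30: 2.80 × √(1/10 + 1/30) = 1.02 SD
- 30 versus 30, for comparison: 2.80 × √(2/30) = 0.72 SD (0.74 SD with the t distribution)

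**Step 3: how often background alone would look like a product effect.** Suppose DiabetEaze does nothing and the two backgrounds differ by d SD on an outcome. A two-sample t-test with 30 per arm has 58 degrees of freedom, critical value 2.00 and noncentrality d × √(30/2) = d × √15 = 3.873d.

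| Assumed d | Noncentrality | Chance of p ≤ 0.05 |
|---|---|---|
| 0 | 0 | 5% |
| 0.2 | 0.77 | 12% |
| 0.3 | 1.16 | 21% |
| 0.5 | 1.94 | 48% |

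The result could credit or debit the product, depending on which background does better.

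**Step 4: the same 120 subjects randomised within background.** This gives 120 / 3 = 40 per background, so 20 versus 20 in each and 60 versus 60 overall. The detectable difference is 2.80 × √(2/60) = 0.51 SD overall (0.52 SD with the t distribution) and 2.80 × √(2/20) = 0.89 SD, about 0.9 SD, within one background.

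**The case against.** The strongest reply is that the protocol never says SOC is a single regimen. Control subjects might each continue their own care, so that Group 3 contains some matched controls for every study group. An analysis plan that is not shown could then compare within background. This stands as a possibility, so it would go too far to infer that no analysis could ever separate product from background. What it would rescue is little: roughly 10 controls per background if evenly split, and nothing in the text secures that split.

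A reader might also infer that the summary and the group list contradict each other over Group 6. They need not: life style management could be that group's SOC, or be given with it. Because SOC is undefined, this is an ambiguity to reconcile, not a demonstrated contradiction.

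Likewise, a reader might conclude that Groups 4 to 6 are not randomised against Group 3. The text says subjects are randomised to the groups; that background is already in place is only one reading.

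Finally, the protocol names no between-group contrasts, calls the study realistic, and refers to a flow chart that is not shown and might describe the arms. Comparing packages with usual care is a conceivable aim. But the stated objectives are about the product, and Group 3 is the only control from which a type 2 diabetes product effect could be drawn.

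**Conclusion.** The point holds as a defect in the group structure, in conditional form. If Group 3's SOC is one regimen, at least two of the three type 2 diabetes contrasts, covering at least 60 of the 120 subjects, combine background with DiabetEaze. If it is a mixture, no study group as a whole has a matched control and only small subset comparisons remain. The figure of 60 should not be quoted without its condition: it is a minimum under the single-regimen reading, becomes 90 if no background matches, and does not apply to a mixture.

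The false-attribution rates of about 12%, 21% and 48% are illustrations. They rest on assumed background differences of 0.2, 0.3 and 0.5 SD, for which the protocol gives no basis. The conclusion also assumes that the three named backgrounds really differ. The pre-diabetes pair, Groups 1 and 2, is not affected. This goes beyond detail that an analysis plan would normally supply, because the groups themselves provide no specified matched control for at least two of the study groups.

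**What to change.** Amend the protocol as follows.

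1. Reconcile Reference Therapy in the summary with the group list under Participant recruitment process, so that the background care of Groups 3 to 6 is stated once and consistently. Which care that is remains the sponsor's choice.
2. State Group 3's background, and whether background is assigned by the randomisation or already in place.
3. Restrict any efficacy claim for DiabetEaze in type 2 diabetes to contrasts in which study and control subjects share the same background. Report the unmatched study groups descriptively.

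This needs no added patients. The cost is that the unmatched study groups lose a product claim.

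Alternatively, if background is already in place, randomise DiabetEaze versus placebo 1:1 within background strata among the same 120 subjects, with a stratified overall contrast of 60 versus 60 (about 0.52 SD detectable at 80% power). The cost is that each background alone has about 20 per arm (about 0.9 SD detectable), which presumes about 40 subjects can be recruited on each. The pooled contrast also averages over backgrounds and would not show an effect that differs between them.

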### **Conduction of trial and Assessments**

#### **Description of type- Design of the trial to be conducted**

The trial is planned as Open, Realistic, Prospective, Randomized, Controlled, Interventional Clinical study. The study will be conducted in six groups of which two groups will be control and rest four will be trial groups. The initial assessment will be done before the commencement of the study (Baseline/0th day) and simultaneously the study will be initiated. Further assessment will be done on the 3rd month and will be followed on every six months till the completion of the study (i.e. 90th, 180th, 365, 545 & 730th day). Interim data analysis will be done at the end of first six months (180th day) and report will be published.

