|                                 | 
given. Placebo for this trial will be given in the similar form as that of the trial drug. Placebo must be consumed according to the same procedures and guidelines as DiabetEaze Powder.
                                                                                                                                                                                                                                                                                                                                                                                                                                                                                                                  |
| CRITERIA FOR EVALUATION: | 
Efficacy:
 
 
• Fasting Blood Sugar
 
• Post Prandial Blood Sugar
 
• Oral Glucose Tolerance Test
 
• HbA1c
 
• Urine Sugar
 
• Investigation for Vitamins & Minerals
 
• Investigations for Diabetic Nephropathy
 
• Investigations for Diabetic Cardiopathy
 
• Investigations for Diabetic Neuropathy
 
• Investigations for Diabetic Retinopathy
 
• Other Laboratory investigations– CBC, Lipid Profile, LFT, RFT, CRP, Urine Examination etc.
 
 
Safety:
 
 
• ADR/AEs using MedDRA
 
• RFT & LFT
 
 |

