## **Serious Adverse Events**

Information about all Serious Adverse Events (SAEs) will be collected and recorded on the SAE Report form within 24 hours of learning of its occurrence. A paper SAE form should be completed by the investigators and faxed or emailed to the Sponsor within 24 hours using the safety reporting contact information provided. An SAE is any undesirable sign, symptom, or medical condition which:

- ❖ Is fatal or life-threatening (i.e. an event with an outcome of ‘Death’), or
- ❖ Requires or prolongs inpatient hospitalization, or
- ❖ Results in persistent or significant disability/incapacity, or
- ❖ Is medically significant, as determined by a qualified health professional, may jeopardize the subject, and may require medical or surgical intervention to prevent one of the outcomes listed above
- ❖ Any adverse event causing the need for unblinding will be handled as a serious adverse event.

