## **Provision of auxiliary care**

In the event of a medical emergency, where it is imperative to know which treatment arm the subject was randomized to in order to make future treatment decisions, the Investigator make necessary arrangement for expert management.

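### The protocol calls the trial open but plans a similar-form placebo and refers to unblinding; masking must be reconciled and stated for each comparison

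*Protocol*

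**What the plan says.** **Open.** The design description states "The trial is planned as Open, Realistic, Prospective, Randomized, Controlled, Interventional Clinical study". The Methodology section repeats it: "Open, realistic, prospective, randomized, controlled, interventional clinical study". The scientific title and the Study Design row of the Clinical Trial Summary carry the same label.

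**Placebo.** Under Reference Therapy, the Summary says "Placebo and Standard of Care (SOC) will be given to control groups". It adds "Placebo for this trial will be given in the similar form as that of the trial drug" and "Placebo must be consumed according to the same procedures and guidelines as DiabetEaze Powder". The group list under Participant recruitment process speaks only of control groups and does not mention placebo.

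**Unblinding.** The Serious Adverse Events section ends its list with "Any adverse event causing the need for unblinding will be handled as a serious adverse event". Provision of auxiliary care deals with a medical emergency "where it is imperative to know which treatment arm the subject was randomized to".

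**Outcomes that depend on judgement.** One primary objective is change in quality of life assessed through direct symptoms. Each adverse event is graded for its relationship to the study drug on a three-level scale. Investigator's judgment is a listed reason for stopping study drug.

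**Numbers.** There are six groups of 30: two controls (Groups 1 and 3) and four study groups (Groups 2, 4, 5 and 6), 180 subjects in all. A p value of 0.05 or less counts as significant.

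**The concern.** These statements cannot all describe the same trial. If treatment is open, nobody needs unblinding, the serious-adverse-event criterion that mentions it can never be met, and the arm is already known in any emergency. If treatment is hidden, the open label is wrong in four places. Two sites could run the trial in opposite ways and each claim to follow the protocol.

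The choice matters for what the results mean. Symptom reports, causality grading and decisions to stop study drug can all shift when subject and investigator know who takes the product. Over 730 days, that knowledge can also change diet, adherence and concomitant medication. Laboratory assays such as HbA1c and fasting glucose are less exposed, because only such changes in behaviour can move them. Read as open, the trial gives up the main protection that a placebo control offers on exactly the outcomes that need it.

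**Working it through.** **1. The plan's own figure.** 6 groups × 30 = 180, which agrees with the stated sample size. The protocol gives no effect size, SD or power, so nothing else can be reproduced.

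**2. The statements side by side.**

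| Where in the protocol | What it implies |
|---|---|
| Summary: Title (Scientific), Study Design | Open |
| Methodology: Type of study design | Open |
| Description of type/design | Open |
| Summary: Reference Therapy | Similar-form placebo, taken in the same way as the product |
| Serious Adverse Events | Treatment is hidden and may need to be revealed |
| Provision of auxiliary care | The arm is not known to those managing the subject |

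Four statements point one way and three the other. No text says who, if anyone, is masked. The flow chart is not shown, so it could not be checked.

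**3. Which comparisons the placebo could mask.**

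- Pre-diabetes: Group 1 and Group 2 are one control and one study group in the same condition. Both receive standard of care under the Summary, so a matched placebo can mask product against no product.
- Type 2 diabetes: Groups 4, 5 and 6 take the product with allopathic medicines, with AYUSH medicines and with lifestyle management respectively. These backgrounds are visibly different. Group 3 receives placebo plus a standard of care that is not described. At most one of the three study groups can share that background, and the protocol does not say which.
- If one does, masking reaches Groups 1, 2, 3 and that group: 4 × 30 = 120 subjects. The other two groups, 2 × 30 = 60 of 180, remain unblinded.

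**4. Illustration of what knowledge of treatment could do.** Inputs: n = 30 per group (protocol); α = 0.05 (protocol; two-sided assumed, as sidedness is not stated); a shift of b standard deviations in a subjective score caused only by knowing the arm (assumed, no source in the protocol); no true effect.

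Two-sample t test, 58 degrees of freedom, critical value 2.002, noncentrality λ = b × √(30/2):

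| b (SD) | λ | Rejection rate |
|---|---|---|
| 0 | 0 | 5.0% |
| 0.2 | 0.775 | 11.9% |
| 0.3 | 1.162 | 20.8% |
| 0.4 | 1.549 | 33.2% |

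The normal approximation gives 12.1%, 21.3% and 34.1% for the last three rows, so the method makes little difference. The assumed b determines the answer.

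**The case against.** **Open may simply be the wrong word.** The placebo and the unblinding text suggest that a blinded trial may have been intended. This stands as a caution: the protocol does not show that anyone chose to give up blinding. It does not remove the problem, because the word appears four times and governs conduct.

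**Not every group can be blinded.** This stands. A fix that called for blinding all six groups would fail, for the reason given by the differing background care.

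**Similar form is not a look-alike.** This also stands. The wording may mean no more than a powder. It does not address colour, taste or smell, and the ingredients include turmeric and cocoa. A reader might infer that a ready blind is being thrown away, but the text shows only that a placebo is planned. Nor is an open placebo useless: it can equalise the daily routine of taking a powder.

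**Allocation concealment.** A reader might take the sentence that "the Sponsor Representative or the Study Investigator will provide the study staff with a unique randomization number for the subject" as a concealment failure. The protocol does not support that. The sentence applies once the subject is randomised, and the same section says that randomisation is central and dynamic. What remains is a blinding point: if the trial is masked, whoever issues the number must not be able to link it to treatment.

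**The percentages have no endpoint behind them.** Correct. No symptom or quality-of-life instrument appears in the efficacy list or the visit schedules, and most listed efficacy measures are laboratory values or investigations.

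**Conclusion.** The contradiction is real and rests on the protocol's own words. It is not a detail that can be left to an analysis plan, because masking governs conduct and cannot be restored once treatment is known. Followed literally, the open label exposes one primary objective, adverse-event relatedness and investigator-judged withdrawal to knowledge of treatment, which a properly matched placebo could prevent in at least the pre-diabetes comparison.

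The size of the bias cannot be estimated from the protocol. The 12% to 33% range is an illustration that depends wholly on an assumed shift of 0.2 to 0.4 SD, and it should not be quoted as a property of this trial. The count of 60 unblinded subjects assumes that one Type 2 diabetes study group does share Group 3's background care; if none does, only Groups 1 and 2 can be blinded.

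**What to change.** 1. Replace the open label in all four places (scientific title, Study Design row, Type of study design, design description) with masking stated per comparison.
2. Make Group 1 versus Group 2 participant-, investigator- and assessor-blind, using coded packs of matched powder. State the placebo in the group list as well as in the Summary.
3. State which Type 2 diabetes study group shares Group 3's background care, and blind that pair in the same way.
4. Label the remaining Type 2 diabetes groups open. Mask the existing outcome assessors where feasible, and interpret these groups' subjective outcomes with the lack of blinding in view.
5. Amend the sentence on issuing randomisation numbers in both places where it occurs (Participant recruitment process and the Day 0 visit), so that whoever issues the number cannot link it to treatment.
6. Reconcile Serious Adverse Events and Provision of auxiliary care with the chosen masking. Neither contains a code-break step at present, so they cannot serve as the procedure as they stand.

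**Cost.** The sample size stays at 180. What is added is coded packing, work to match the placebo's appearance and taste, and code-break logistics. The protocol gives no costs, so these cannot be priced. The price in evidence is that two Type 2 diabetes groups (60 of 180 subjects) stay open, with weaker claims on subjective outcomes.
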